## Abstract

**Background:**

Lymphoedema is a common and troublesome condition that develops following breast cancer treatment. The aim of this study is to analyze the effectiveness of Manual Lymphatic Drainage in the treatment of postmastectomy lymphoedema in order to reduce the volume of lymphoedema and evaluate the improvement of the concomitant symptomatology.

**Methods:**

A randomized, controlled clinical trial in 58 women with post-mastectomy lymphoedema. The control group includes 29 patients with standard treatment (skin care, exercise and compression measures, bandages for one month and, subsequently, compression garnments). The experimental group includes 29 patients with standard treatment plus Manual Lymphatic Drainage. The therapy will be administered daily for four weeks and the patient's condition will be assessed one, three and six months after treatment.

The primary outcome parameter is volume reduction of the affected arm after treatment, expressed as a percentage. Secondary outcome parameters include: duration of lymphoedema reduction and improvement of the concomitant symptomatology (degree of pain, sensation of swelling and functional limitation in the affected extremity, subjective feeling of being physically less atractive and less feminine, difficulty looking at oneself naked and dissatisfaction with the corporal image).

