The third published randomized trial, involving 42 women with modest stage I or II lymphoedema compared standard therapy alone with standard therapy plus MLD and training in self-massage (level I evidence). Standard therapy included the use of a custom-made sleeve-and-glove compression garment worn during the day, instruction in physical exercises, education in skin care, and information and recommendations about lymphoedema. Both groups obtained a significant reduction in limb volume, a decrease in discomfort and increased joint mobility over time. However, no significant differences in objective measures regarding change in arm volume or subjective measures of symptoms related to lymphoedema were found between the 2 groups [18]. This study investigated the effect of eight sessions of MLD over two weeks, so the MLD course was relatively short and the study group was limited to those with mild to moderate swelling (20-30% of difference). Information about quality of life was gathered using the questionnaire EORT QLQ-C30, but the results were not considered in the final evaluation. On the other hand, there is no evidence that shows that the effect of MLD is permanent - because previous studies measured the volume directly after the conclusion of MLD - or if the MLD can be effective in decreasing the symptoms, in spite of not obtaining an improvement in volume reduction. Therefore, the utility of MLD as part of the Physical Complex Therapy has turn out to be relevant, given the exclusive dedication of the therapist that it entails and the extra cost in relation to the potential health benefits for patients.

The aim of this study is to analyze the short-term and long-term effectiveness of Manual Lymphatic Drainage (MLD) in the treatment of postmastectomy lymphoedema in order to reduce the volume of lymphoedema and evaluate the improvement of the concomitant symptomatology.

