### Subjects of study

Caucasian women with lymphoedema who have undergone a prior mastectomy, tumorectomy or quadrantectomy and axillary lymphadenectomy. A sample size of 58 patients randomized in 1:1 ratio (29 per group) will be required.

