### Inclusion criteria

• Women older than 18 years treated for unilateral breast cancer with ipsilateral axillary lymphadenectomy.

• Patients with ipsilateral lymphoedema with a limb volume difference of at least 200 ml compared to the lateral member.

• Patients who have finished treatment with radiotherapy and/or chemotherapy at least six months before the study begins.

• Informed consent must be signed

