#### Secondary Outcomes

The results of the Spanish validated quality of life questionnaires, EORTC QLQ-C30 version 2.0 for cancer in general and EORTC QLQ-BR23 specific for breast cancer, are used to assess the efficacy of the treatment, measuring the improvement of the lymphoedema concomitant symptomatology. Particularly, the items of the latter referring to the upper extremity (47, 48, 49) and to the corporal image (39, 40, 41, 42) are analyzed and the higher the score, the worse the result.

The secondary outcomes include:

• Degree of pain in the affected upper extremity

• Degree of sensation of swelling in the affected upper extremity

• Degree of functional limitation in this extremity

• Subjective feeling of being physically less atractive

• Subjective feeling of being less feminine

• Difficulty looking at oneself naked

• Dissatisfaction with the corporal image

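### The aim and abstract name postmastectomy lymphoedema, but eligibility also admits breast-conserving surgery; the label should match the enrolled population, and surgery type should be a fixed covariate for the body-image items

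*Protocol article*

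**What the plan says.** The article gives the population in two ways.

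- **Aim and abstract.** The abstract's Background paragraph states: "The aim of this study is to analyze the effectiveness of Manual Lymphatic Drainage in the treatment of postmastectomy lymphoedema". The aim that closes the main Background section again refers to the "effectiveness of Manual Lymphatic Drainage (MLD) in the treatment of postmastectomy lymphoedema". The abstract's Methods paragraph reads: "A randomized, controlled clinical trial in 58 women with post-mastectomy lymphoedema".
- **Eligibility.** Subjects of study defines the sample as "Caucasian women with lymphoedema who have undergone a prior mastectomy, tumorectomy or quadrantectomy and axillary lymphadenectomy". The first inclusion criterion reads: "Women older than 18 years treated for unilateral breast cancer with ipsilateral axillary lymphadenectomy". Neither makes mastectomy a condition of entry.

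The primary outcome is percentage volume reduction in the affected arm. Seven symptom items are listed under Secondary Outcomes. Four of them concern body image: feeling less attractive, "Subjective feeling of being less feminine", difficulty seeing oneself undressed, and dissatisfaction with one's body.

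Under Statistical methods, baseline comparability is tested first. Linear or logistic regression follows only if that comparison shows a need for it, and no covariates are named.

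**The concern.** A woman treated by quadrantectomy or tumorectomy with axillary lymphadenectomy can be randomised, yet she lies outside the population that the aim and abstract name. If the report repeats the aim's wording, readers will take the result as evidence about lymphoedema after mastectomy when an unstated share of the sample had conserving surgery.

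For arm volume this is a matter of labelling. For the body-image items there is a second, smaller issue. Whether the breast was removed or conserved plausibly influences how a woman answers, whatever happens to her arm. The article's own Background says that the QLQ-BR23 assesses the influence of surgery on body image, among other things. In a trial of this size a factor of that kind can be unevenly split by chance, and adjustment is left to depend on a baseline test.

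**Working it through.** **1. The texts side by side**

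| Place | Surgery named or required |
|---|---|
| Abstract, Background (aim) | mastectomy |
| Abstract, Methods | mastectomy |
| Main Background, closing aim | mastectomy |
| Subjects of study | mastectomy, tumorectomy or quadrantectomy, with axillary lymphadenectomy |
| Inclusion criteria | axillary lymphadenectomy; type of breast surgery not restricted |

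The enrolled population is wider than the named one and contains it. No section defines the postmastectomy label so as to include conserving surgery. The Background elsewhere uses the wider term of breast cancer-related lymphoedema.

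**2. Inputs for the chance-imbalance check**

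- From Sample Size: 29 randomised per arm; 20 per arm remain after the planned 30% dropout (20/0.70 = 28.6, rounded up to 29).
- Assumed, because the article gives no figure: a mastectomy share of 50%, with 30% and 70% as a range.

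**3. Chance difference in mastectomy share between arms**

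SD = sqrt(2 × p(1 − p)/n)

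- p = 0.5, n = 29: sqrt(2 × 0.25/29) = 0.131, so 13 points. The 95% range is ±1.96 × 0.131 = ±0.257, about 26 points. The expected absolute gap is about 0.80 × 13.1 = 10.5 points.
- p = 0.3 or 0.7, n = 29: sqrt(2 × 0.21/29) = 0.120, so 12 points, with a 95% range of about ±24 points.
- p = 0.5, n = 20: sqrt(2 × 0.25/20) = 0.158, with a 95% range of about ±31 points.

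**4. Would the baseline comparison detect such a gap?**

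The article does not say what makes adjustment necessary. If it means p < 0.05:

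| Mastectomies per arm | Gap | Chi-square p (uncorrected) | Fisher p |
|---|---|---|---|
| 11/29 vs 18/29 | 24 points | 0.066 | 0.11 |
| 10/29 vs 18/29 | 28 points | 0.036 | 0.065 |

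A gap of 24 points would pass unadjusted under either test, and one of 28 points would pass under Fisher's test.

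**5. What a gap could do to a body-image comparison**

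Shift = gap × difference between surgery types. The article gives no such difference. Assume 10 to 20 points on a 0–100 scale, which is also an assumption because the article lists single items.

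- Expected gap of 10.5 points: 0.105 × 10 = 1.0 to 0.105 × 20 = 2.1 points.
- Edge of the 95% range, 25.7 points: 0.257 × 10 = 2.6 to 0.257 × 20 = 5.1 points.

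These shifts apply to a comparison of post-treatment levels. A stable surgery-related difference already present at baseline would largely cancel in change from baseline.

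**The case against.** The case for leaving the text alone has four parts.

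- **Who is enrolled is clear.** The eligibility text is explicit, mastectomy patients are included, and every participant has had axillary lymphadenectomy and has a volume difference of at least 200 ml. This stands, and it keeps the point minor. A reader might infer from the mismatch that the result will not apply to women after mastectomy. The article does not support that: those women are in the sample, and nothing in it suggests that the effect on arm volume varies with breast surgery.
- **Randomisation protects the comparison.** Surgery type is settled before 1:1 allocation, so it can differ between arms only by chance, and the planned confidence intervals already allow for chance. This also stands. A reader might infer that the body-image comparisons are biased by surgery type; they are not biased systematically.
- **Adjustment is already provided for.** The regression step could take in surgery type, so it would be wrong to say that the article ignores the matter. Naming covariates for secondary outcomes is also commonly left to an analysis plan. What remains is that the article does fix a rule, namely adjustment triggered by a baseline comparison, and that rule is insensitive at 29 per arm.
- **The score shifts rest on assumptions.** This is correct. The mix, the size of the surgery effect and the scale are not in the article, and a typical imbalance gives shifts less than half those at the edge of the 95% range.

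**Conclusion.** The inconsistency is real: three statements name postmastectomy lymphoedema, and the two eligibility sections admit conserving surgery as well. The result will describe a mixed-surgery population that includes mastectomy patients and cannot be reported as specific to the postmastectomy group. For the primary outcome this is a labelling error with no effect on validity or sample size.

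For the four body-image items the residual issue is chance imbalance, with an SD of about 13 points under an assumed 50:50 mix. The test-triggered adjustment can miss a gap of about 24 points, if the trigger is read as p < 0.05. Any resulting score shift depends on figures that the article does not give, so the ranges in the working are illustrations, not estimates. Severity is minor.

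**What to change.** 1. Reword the aim (abstract and main text) and the abstract's Methods paragraph to refer to lymphoedema after breast cancer surgery, whether mastectomy or breast-conserving, with axillary lymphadenectomy.
2. Report surgery type by arm in the baseline table.
3. For the four body-image items, prespecify surgery type (mastectomy or conserving) and the baseline item score as covariates, in place of adjustment that waits on a baseline comparison. The protocol has a quality-of-life questionnaire completed before outpatient treatment starts, and surgery type should be known from the eligibility check and medical history.

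**Cost.** Three wording changes, one row in a table and two covariates in secondary analyses. Eligibility, treatment, primary outcome and the planned 58 patients stay as they are. The claim becomes broader and gives up its specificity to mastectomy.

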**Discussion:**

The results of this study will provide information on the effectiveness of Manual Lymphatic Drainage and its impact on the quality of life and physical limitations of these patients.

**Trial registration:**

ClinicalTrials (NCT): NCT01152099

## Background

Nowadays, breast cancer is the most frequent malignancy in women, with an incidence of 35-44 new cases per 100.000 women/per year, and its frequency is increasing. Approximately 25% of breast cancer patients develop lymphoedema following breast cancer treatment, and the risk increases every year [1]. Thus, breast cancer-related lymphoedema is one of the main complications and most dreaded sequela of breast cancer and its therapies, and can have long-term physical and psychosocial consequences for patients. It consists of the accumulation of lymph in the interstitial spaces, principally in the subcutaneous fatty tissues, caused by a defect in the lymphatic system. It is marked by an abnormal increase of tissue proteins, oedema, chronic inflammation and fibrosis [2]. Three stages of lymphoedema have been described. Stage I presents with pitting and is considered reversible; some women in this stage have no increased arm girth or heaviness and no signs of pitting oedema. As the oedema progresses, it becomes brawny, fibrotic, non-pitting and irreversible (stage II). In advanced lymphoedema (stage III), which rarely occurs following breast cancer treatments, cartilaginous hardening occurs, with papillomatous outgrowths and hyperkeratosis of the skin. Problems associated with lymphoedema include: pain, altered sensations such as discomfort and heaviness, difficulties with physical mobility, physiological distress, recurrent infections and social isolation [3,4]. Lymphoedema has been shown to significantly negatively affect quality of life, [5] and it is a traumatic condition because apart from the inconveniences and functional impairment that starts at the arm level, the aesthetic factor plays a determinant role in the loss of self-esteem, which causes psychological sequelae in many patients [6]. Some quality of life scales are available to determine how the affected patients define, admit and explain their personal experience regarding the symptoms they experience and in which way these symptoms have an influence on the degree of functionality regarding daily activities and interpersonal relationships. In 1980 The European Organization for Research and Treatment of Cancer (EORT) created a group to study the quality of life in patients with cancer and developed the EORT Quality of Life Questionnaire (EORT QLQ-C30). Subsequently EORT QLQ-BR 23 was developed to assess the specific aspects of lymphoedema in patients with breast cancer. The latter evaluates the influence of surgery, chemotherapy, radiotherapy and hormone therapy on the homolateral arm of the treated breast, the corporal image, sexuality, perspectives of future, symptoms of the disease and function of the upper extremity, evaluating a total of 23 items. Both questionnaires are validated for the Spanish population [7]. In a study in which 744 patients with breast cancer were assessed with these quality of life scales, some imbalances regarding the quality of life in those patients with lymphoedema were found [8]. Definitively, lymphoedema is one of the most severe sequelae that affects health-related quality of life in treated breast cancer patients.

Lymphoedema treatment remains a problem even with modern treatment modalities, since clear therapeutic protocols do not exist. Several methods have been used with varying results. Among them the physical treatment introduced by Winiwarter (1892), improved by Vodder (1932-1960) and later named Complex Physical Therapy (CPT) by Foldie, has been recommended by several groups of experts [9]. Complex Physical Therapy, also called Complex Decongestive Physiotherapy, is a treatment regimen that includes meticulous skin hygiene, manual lymph drainage, bandaging, exercises and supportive garments. This therapy is carried out in two phases; in the first phase (treatment), the aim is to mobilize the lymph accumulated, reduce the fibrous tissue and improve the health of the skin using mainly daily Manual Lymph Drainage (MLD) during a variable period of time. In addition, patients receive instructions regarding skin care, prophylactic measures and the use of multilayer bandages. In the second phase (maintenance), compression bandaging, regular physical exercise and weight control are used [10].

Although the first results have been optimistic, in randomized controlled clinical trials, the CPT has not clearly demonstrated any superiority when compared with other simpler alternatives and no study has evaluated patients' treatment preferences or the effects of the treatment on quality of life [11]. Several authors suggest that this technique should be reserved only for selected cases. The proof of concept for using CPT to stimulate the lymph drainage has a profound physiological basis, but the quality of evidence on the relative effectiveness of therapies is poor. On the other hand, the fact that CPT implies several techniques (manual lymph drainage, skin care and multilayer compression bandaging followed by a compression garment to reduce oedema and therapeutic exercises) makes it difficult to recognize which of them is the truly effective one in the treatment of lymphoedema [12-14].

Manual Lymph Drainage (MLD) is a massage technique that involves the skin surface only and follows the anatomic lymphatic pathways of the body. A session of manual lymph drainage starts centrally in the neck and trunk to clear out the main lymphatic pathways, thereby facilitating drainage from the arm. Unlike other types of massage, it produces neither blush nor pain and it does not even have a stimulant effect. To successfully complete this technique, a knowledge of the anatomical distribution of the lymphatic and superficial ganglions and of their interconnections is necessary. The MLD is carried out in a descending manner to facilitate the flow of the lymph from the affected areas to those not affected. It is possible to carry out MLD in the case of late or latent lymphoedema three days postsurgery if contraindications do not exist. There are several schools (Vodder, Leduc, Foldie), but they all agree on the fundamental aspects. The MLD must be applied by a physical therapist trained for it. Its application demands a long period of time (from 45 to 60 min.) and it is usually performed once a day (four or five times a week) for 2 to 4 weeks. A study carried out by Leduc and Colls demonstrated that the greatest reduction of the oedema is obtained in the first week of treatment; during the second week the results became stable [15].

The results from several case studies (including over 400 patients) clearly showed that treatment with MLD and compression bandaging had a volume-reducing effect. However, the interpretation of these results is limited due to the methodology used, and their design did not offer the possibility to investigate the extent to which MLD treatment contributed to the reduction of lymphoedema.

Only three small, randomized, controlled trials have assessed MLD for arm lymphoedema but contradictory results have been found. Two of the studies showed statistically significant differences in the reduction of oedema that favored the group on combined treatment with MLD, despite the fact that in one of the studies, MLD was only administered for one week. The first study, conducted in 35 women, compared compression bandaging plus MLD with compression bandaging alone (level III evidence) [16]. There was a trend in mean volume reduction and a statistically significant difference between the 2 groups in the percentage reduction in volume in favour of the combined treatment. In the second trial, Manual Lymph Drainage plus a compression garment use was compared with sequential pneumatic compression plus compression garment use; no difference was detected between the treatment groups (level II evidence) [17].

The third published randomized trial, involving 42 women with modest stage I or II lymphoedema compared standard therapy alone with standard therapy plus MLD and training in self-massage (level I evidence). Standard therapy included the use of a custom-made sleeve-and-glove compression garment worn during the day, instruction in physical exercises, education in skin care, and information and recommendations about lymphoedema. Both groups obtained a significant reduction in limb volume, a decrease in discomfort and increased joint mobility over time. However, no significant differences in objective measures regarding change in arm volume or subjective measures of symptoms related to lymphoedema were found between the 2 groups [18]. This study investigated the effect of eight sessions of MLD over two weeks, so the MLD course was relatively short and the study group was limited to those with mild to moderate swelling (20-30% of difference). Information about quality of life was gathered using the questionnaire EORT QLQ-C30, but the results were not considered in the final evaluation. On the other hand, there is no evidence that shows that the effect of MLD is permanent - because previous studies measured the volume directly after the conclusion of MLD - or if the MLD can be effective in decreasing the symptoms, in spite of not obtaining an improvement in volume reduction. Therefore, the utility of MLD as part of the Physical Complex Therapy has turn out to be relevant, given the exclusive dedication of the therapist that it entails and the extra cost in relation to the potential health benefits for patients.

The aim of this study is to analyze the short-term and long-term effectiveness of Manual Lymphatic Drainage (MLD) in the treatment of postmastectomy lymphoedema in order to reduce the volume of lymphoedema and evaluate the improvement of the concomitant symptomatology.

## Methods

### Study Design

Single centre, randomized, controlled study of two Physical Complex Therapies. The total follow-up period per patient is 6 months.

### Sample Size

For the calculation of the sample size we make the following assumptions:

• The effect of the standard treatment on the control group will cause an average limb volume reduction of 5%.

• The effect of the treatment on the experimental group will cause an average limb volume reduction of 25%

• We also assume that the standard deviation will be similar in both groups and near to 25%. With this information and with an alpha risk of 0.05 and a power of 0.80, the calculation of the sample size is 20 patients in each group. Considering a 30% dropout rate in each group, the corrected sample size is 58 patients randomized in two groups of 29 patients each.

